# Trial Enrollment

There is no randomization or blinding protocol for this study as there is no therapeutic intervention.

- 1. Screening Procedures

The Principal Investigator at each clinic site (or designee) and the study coordinator will have responsibility for subject recruitment including a chart review to identify potentially eligible subjects. All screening must comply with the local institution’s Health Insurance Portability and Accountability Act (HIPAA) requirements. Subjects may be screened for eligibility more than once during the accrual period.

- 1. Subject Enrollment and Site Enrollment caps

Subjects will be enrolled based on the definitions listed under inclusion and exclusion criteria. As treatment patterns differ between institutions, the study aims for a broad recruitment over a number of sites rather than 1 or 2 sites dominating the subject pool. This aim is balanced by the logistical concern of not significantly hampering recruitment in a rare disease. Subject caps will be lifted 3 months after the first subject is enrolled in the study. To enable recruitment to proceed smoothly, sites will be able to access real-time recruitment information by cohort via the web through the data management system (ADEPT). The distributions of sex and age of SMA cases will be monitored regularly, and the plan for recruitment of controls of appropriate sex and ages may be altered in order to match distributions.

The following subjects caps (maximum number of subjects allowed per site) for each cohort are defined below:

Table 1: Subject Caps Per Site

|  | Total subjects | Subject Cap per site |
| --- | --- | --- |
| Type I | 15 | 5 |
| Type II | 45 | 10 |
| Type III | 40 | 10 |
| Controls | 20 | 7 |
| TOTAL | 120 |  |

- 1. Replacement of Subjects

Subjects may be replaced by additional subjects in the same cohort prior to the close of the enrollment period if:

- Subject’s specimen(s) collected are lost in transit.
- Subject’s specimen(s) are broken upon receipt.
- Subject’s specimen(s) are compromised or unanalyzable (i.e. hemolyzed) upon receipt.
- Specimens of a particular type do not meet minimum volumes for processing.
- No specimens of a particular type are collected during the visit.
- Study assessments required for the primary or secondary outcome are not collected.

Any clinical data collected or usable specimens for the subjects replaced may be analyzed and used in the statistical analysis.

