# STUDY POPULATION

Three groups of SMA patients and one cohort of control children will be enrolled according to the classifications below:

- Children with type I SMA (n=15).
- Children with type II SMA (n=45).
- Children with type III SMA (n=40).
- Control subjects (n=20) will match the gender and age distribution expected in the SMA cohorts. Control children may be either confirmed non-carrier, genetically- related siblings of SMA children or unrelated children (limit 1 child per family for enrollment in the control cohort).
- n=5 Females age 2-5.
- n=5 Females age 6-12.
- n=5 Males age 2-5.
- n=5 Males age 6-12.
- SMA subjects will be enrolled from approximately 15 academic pediatric neuromuscular clinics.
- Control subjects will be enrolled from pediatric neuromuscular clinics as well as referring pediatric practices within the same institutions.
  1. Inclusion Criteria

For all groups:

1. Age 2 to 12 years, inclusive.
2. In good health (other than SMA) in the judgment of the clinical investigator at the time of assessment.

SMA group requirements:

1. Documented homozygous deletion of SMN1 (exon 7). Genotyping results must be performed by a CLIA certified laboratory and documented via chart review.
2. SMA type I defined as the inability ever to sit unaided in the judgment of the clinical investigator.
3. SMA type II defined as the ability to ever sit unaided for >30 seconds on a flat surface in the judgment of the clinical investigator.
4. SMA type III defined by the ability to ever stand unaided for 30 seconds and walk unaided for >30 ft in the judgment of the clinical investigator.

Control group requirements:

1. Otherwise healthy children that may be either genetically-related siblings of SMA children (genetically confirmed non-carriers), or unrelated children. Only one sibling per family with an SMA subject may be enrolled (includes related and unrelated siblings).
   1. Exclusion Criteria

For all groups:

1. Systemic or specific-organ illness, including renal, hepatic, cardiac, pulmonary, significant gastrointestinal illness, hematologic or rheumatic disorders requiring ongoing treatment or chronic medication use.
2. Any known genetic condition other than Spinal Muscular Atrophy requiring pharmaceutical treatment.
3. Use of any putative SMN-enhancing medications or treatments for 14 days prior to enrollment including, valproic acid, phenylbuterate, and hydroxyurea.

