In order to find disease-specific biomarkers, comparison of biomarkers between SMA and control cases will be performed using regression analysis, controlling for sex and age. Correlations of biomarkers with outcomes will be conducted within SMA cases, as well as in the combined population of SMA and control cases.

To model the correlation of each individual biomarker with the Modified Hammersmith Functional Motor Scale, univariate regression analyses will be performed, controlling for sex and age. Additionally, elastic net multivariate regression (25) will be used to find a composite set of biomarkers that correlates with outcome.

Univariate regression and elastic net multivariate regression will also be used for continuous secondary outcomes (e.g., age of disease onset, height, weight). For categorical outcomes (e.g., SMA type), analysis of variance (ANOVA), controlling for sex and age, will be performed to discover individual biomarkers that vary by outcome. Likewise, PAM (Prediction Analysis of microarrays) (26) will be used to try to find a composite set of biomarkers that varies by outcome.

In all analyses a p-value ≤ 0.05 will be considered statistically significant. The false discovery rate (27) will also be controlled. If there is an extensive amount of missing data, or data appears not to be missing completely at random, then multiple imputations will be considered. Standard statistical software packages (e.g., SAS) will be used.

- 1. Interim Analysis

No interim analysis for safety or efficacy will be performed during this study.

- 1. Potential Risks and Benefits

Potential risks to study subjects are minimal. Blood will be drawn in volumes that are approximately half (or less than half) of the maximum blood draw allowed for children (by weight) (28) (29). SMN2 copy number will be genotyped from DNA specimens for all cohorts. SMN1 gene analysis will only be done on those control subjects with no genetic relationship to SMA children. SMA subjects will be pre-diagnosed and therefore no further risks are anticipated from a genetic point of view. The control subjects may opt out of the DNA portion (SMN1 gene analysis) of the study. The control subject’s risk is that the study does not benefit the individual directly.

Potential benefits are that study subjects will benefit from the satisfaction that they are participating and contributing to SMA research.

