The risk/benefit ratio is favorable since participation in the study is reasonably commensurate to routine care for an SMA subject over the course of one visit.

- 1. Limitations of the Study

Several limitations were considered in the design of the study.  Outlined below is how the study proposes to mitigate these limitations:

1. Biomarkers may vary by age and Type I subjects will be on the younger end of the age distribution.  The proposed solution is to control for age in all statistical models.
2. Based on the inclusion criterion for age, the study outcomes may not be generalization to children <2 or >12 years old. The primary outcome is not reliable in children less than 2 years of age. Any putative biomarkers identified in this effort would need to be validated in follow-on studies in a broader age distribution.
3. The sample size selected is based on number of specimens collected and it is possible that less than 100% of specimens collected will be analyzable. The study will allow for replacement of subjects to account for these specimens.
4. There is a potential that differences in standards of care between centers or regional differences (in diet or lifestyle) may have an impact on putative biomarker levels  It is unknown whether this has an effect prior to identification of a biomarker.  An ideal biomarker would be robust against effects of lifestyle and diet. The study design attempts to mitigate this potential effect by instituting site caps by cohort.
5. Recruitment of control children may be difficult as they do not have a direct or indirect benefit (other than siblings) from the study.  It is possible that this will be an issue; however the pool of control children is significantly larger than the SMA pool and therefore 20 control individuals is achievable.

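### Section 11.5 relies on site caps against between-center differences, but section 5.2 lifts the caps after 3 months and the section 11.2 models adjust only for sex and age

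*Protocol*

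**What the plan says.** Section 5.2 notes that treatment patterns differ between institutions and states an aim of broad recruitment "rather than 1 or 2 sites dominating the subject pool". Table 1 caps each site at 5 Type I, 10 Type II, 10 Type III and 7 control subjects, against cohort totals of 15, 45, 40 and 20. The section then says: "Subject caps will be lifted 3 months after the first subject is enrolled in the study". It gives its reason: "This aim is balanced by the logistical concern of not significantly hampering recruitment in a rare disease".

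Section 11.5, item 4, recognizes that between-center differences in standard of care, or regional differences in diet or lifestyle, could affect putative biomarkers. Its remedy is: "The study design attempts to mitigate this potential effect by instituting site caps by cohort". It does not mention that the caps expire.

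In section 11.2, disease-specific markers are sought as follows: "comparison of biomarkers between SMA and control cases will be performed using regression analysis, controlling for sex and age". For the primary outcome, "univariate regression analyses will be performed, controlling for sex and age". The ANOVA for categorical outcomes has the same two covariates. No covariates are named there for elastic net or PAM. On the number of centers, section 4 says: "SMA subjects will be enrolled from approximately 15 academic pediatric neuromuscular clinics".

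**The concern.** The protocol identifies a source of confounding, assigns it to one safeguard, and removes that safeguard early. The clock is study-wide and starts with the first subject anywhere, so a site that opens more than 3 months later is never capped. Item 1 of section 11.5 deals with age by putting it in the statistical models. Item 4 deals with center through recruitment limits instead, so nothing stated in the analysis takes over when the limits end.

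If a cohort is concentrated in a few centers, a center-level shift in analyte levels can look like a disease or severity marker. Such a shift may move many analytes together. False discovery rate control takes the p-values as valid and does not remove confounding.

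**Working it through.** **Inputs.** Cohort totals and caps: Table 1, section 5.2. About 15 sites: section 4. Covariates: section 11.2. The documents give no site intraclass correlation (ICC), so 0.05, 0.10 and 0.20 are assumed.

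**Table 1 total.** 15 + 45 + 40 + 20 = 120, as printed.

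**Fewest sites that can fill a cohort under the caps** (total ÷ cap, rounded up):
- Type I: 15/5 = 3
- Type II: 45/10 = 4.5, so 5
- Type III: 40/10 = 4
- Controls: 20/7 = 2.86, so 3

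Once the caps are lifted, the minimum is 1 for every cohort.

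**Largest share from a few sites under the caps.** One site: 5 + 10 + 10 + 7 = 32 of 120 (27%). Two sites: 64 of 120 (53%). An even spread over 15 sites would be 8 per site. Two sites can therefore supply a majority while the caps apply.

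**Error of an SMA-control test without a site term.** Scale total analyte variance to 1, with a fraction ICC between sites. Let w be the difference at each site between its share of controls and its share of SMA subjects. The unadjusted test assumes variance 1/100 + 1/20 = 0.06. The actual variance is ICC × Σw² + (1 − ICC) × 0.06. With R = actual ÷ 0.06, the true error at nominal 5% is 2 × [1 − Φ(1.96/√R)]. SMA subjects are spread evenly, 1/15 per site, unless stated.

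*Controls from three sites (7, 7, 6).* Σw² = 2 × (0.35 − 0.0667)² + (0.30 − 0.0667)² + 12 × 0.0667² = 0.2683. For ICC 0.10, R = (0.02683 + 0.054)/0.06 = 1.347, so the error is 9.1%.

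*Controls from one site.* Σw² = 1 − 1/15 = 0.9333. For ICC 0.10, R = (0.09333 + 0.054)/0.06 = 2.456, so the error is 21.1%.

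*Controls spread evenly, or in proportion to cases.* Σw² = 0, so R = 1 − ICC.

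*Controls spread equally over seven sites.* Σw² = 1/7 − 1/15 = 0.0762.

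*Controls 7, 7, 6 at three sites that each also enrol 20 SMA subjects, the other 40 spread over 12 sites.* Σw² = 2 × (0.35 − 0.20)² + (0.30 − 0.20)² + 12 × (0.0333)² = 0.0683.

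| Where controls come from | ICC 0.05 | ICC 0.10 | ICC 0.20 |
|---|---|---|---|
| Three sites | 7.0% | 9.1% | 13.2% |
| One site (possible once caps are lifted) | 13.6% | 21.1% | 32.2% |
| Even, or in proportion to cases | 4.4% | 3.9% | 2.8% |
| Seven sites | 5.2% | 5.3% | 5.6% |
| Three sites with 20 SMA subjects each | 5.1% | 5.2% | 5.3% |

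A simulation of 20,000 null analytes agrees with the first two rows: 7.2/9.5/12.9% for three sites and 13.8/21.4/32.6% for one.

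**Precision with a random site intercept, controls from three sites.** The standard error is about 0.26 SD, against √0.06 = 0.245 SD reported by the unadjusted test. The 0.245 is too small in this case. The unadjusted difference really has standard error √(ICC × 0.2683 + (1 − ICC) × 0.06), which is 0.265, 0.284 and 0.319 SD at the three ICC values.

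**The case against.** **A declared trade-off.** Section 5.2 openly weighs the caps against recruitment in a rare disease. That stands, and the early lift is not an oversight. But item 4 of section 11.5 does not carry the trade-off through.

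**The SAP may include site.** It may; it is not shown. The firm part of the finding is the mismatch between sections 5.2 and 11.5. The site term is recommended because section 11.2 itself lists the covariates and because adding site is cheap.

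**The error rates need an adverse allocation.** This stands. They pair concentrated controls with evenly spread cases and an assumed ICC. The last three table rows show that inflation nearly or wholly disappears under other allocations. Controls are to come from the same institutions as cases (section 4), which makes the worst patterns less likely but does not exclude them.

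Stronger readings are tempting but not supported:
- A reader might infer that the caps are the only guard against any site effect. Section 10.1 provides central training in assessments and specimen handling. Sections 10.5 and 10.6 track specimens and record processing times and temperatures. Section 10.2 lists case-control matching and within-site group balance as functions of the data system, although no balance requirement is defined. The caps are the only mitigation named for differences in care, diet and lifestyle.
- A reader might infer that three sites can fill any cohort. Under the caps that is true of Type I and controls only.
- A reader might take "There is no randomization or blinding protocol for this study as there is no therapeutic intervention" to mean that laboratories are unmasked and assays run in enrolment order. The sentence gives the absence of treatment as its reason and does not address laboratory work. Section 12.4 restricts specimen labels to collection date, random barcode and subject number, so the label does not show cohort. The protocol says nothing about run order.

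**Conclusion.** The point holds in limited form. Section 11.5 relies on a safeguard that section 5.2 ends 3 months after the first enrolment. While in force, that safeguard allows two sites to supply 53% of subjects. No model in the protocol adjusts for site. Site can therefore confound the SMA-control and severity comparisons.

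The size depends on how the cohorts turn out to be distributed over sites and on an ICC the documents do not give. Across the assumed range, the error of a nominal 5% SMA-control test runs from no inflation, through 7.0% to 13.2% with controls at three sites, to 13.6% to 32.2% with controls at one. These are illustrations of what the text permits, not predictions. The study is a pilot whose candidate markers are to be validated later, so the likely harm is false leads rather than a wrong treatment decision. The change is still worth making because it is cheap.

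**What to change.** 1. In section 11.2, add site as a random intercept to the univariate regressions and the ANOVA, alongside sex and age.
2. For elastic net and PAM, add leave-site-out validation as a check that the selected composite sets do not depend on individual centers.
3. Amend section 11.5, item 4, to say that the caps expire 3 months after the first enrolment and that site is handled in the analysis.

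The caps and their lifting can stay as they are, so recruitment is unaffected, and no new data are needed. The cost is wording plus a small apparent loss of precision: about 0.26 SD against a naive 0.245 SD with controls at three sites. If controls came from a single site, the adjusted comparison would lean mainly on the cases at that site and the loss would be larger. The distribution of cohorts over sites should therefore be reported with the results.

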# STUDY PROCEDURES

- 1. Informed Consent / Informed Assent

Signed and dated IRB-approved informed consent must be obtained from the subject’s parent or guardian before any study-specific screening procedures are performed. The Principal Investigator or approved designee will obtain informed consent from the parent or guardian and an informed assent from the pediatric subject (according to local institutional IRB guidelines) after full review of the pros and cons of the study. The possible benefits and complications of participation will be explained in detail. Every effort will be made to ensure that the subject and parent/guardian fully comprehend the nature of the study and the details of his or her participation. A copy of the consent form will be provided to the parent/guardian and subject. The informed consent process must be documented in the subject’s medical chart.

- 1. Schedule of Study Measurements

Subjects will be screened for eligibility according to the inclusion/exclusion criteria and then will be enrolled and have additional study evaluations on the same day. The purpose of the screening is to identify eligible subjects and to eliminate evidently unsuitable subjects before the enrollment process is started. In some instances, at the site’s discretion, the screening may occur on a separate day than study procedures (for example to confirm carrier status of siblings of SMA subjects). It is anticipated that the duration for all the screening and study procedures will be between 2-4 hours.

- 1. Screening Procedures

Each clinical site will maintain a Screening Log of all subjects screened for the trial. This log will record the reason for any screen failure. Confidentiality of subject data will be maintained throughout the trial. No patient identifiers will be used and all data entered into the trial database will be under code.

All screening procedures are the same for the SMA subjects and the control group.

1. Medical review of inclusion and exclusion criteria.
2. Temperature.
3. Those subjects deemed eligible by the Principal Investigator or designee will complete additional evaluations for Enrollment.
   1. Study Procedures

All study procedures are the same for the SMA subjects and the control group with the exception of collection of DNA for SMN1 genotyping for control subjects only (refer to 6c below).

1. Medical history including motor milestones, age of disease onset for children with SMA, loss of motor function (sitting, ambulation) for children with SMA.
2. Physical Examination including Neurological assessment ,vital signs: sitting BP, pulse and respirations and height, weight and ulnar length.
3. Nutritional assessment by Principal Investigator or designee:
4. Triceps skin fold thickness.
5. Nutritional status question about level of solid food intake.
6. Motor function assessment
7. Modified Hammersmith Functional Motor Scale.
8. 10-meter Timed Walk Test (ambulatory subjects only).
9. Pulmonary assessment
10. Standardized question about level of respiratory support.
11. Forced Vital Capacity (FVC) when subject is greater or equal to 5 years.
12. Specimen acquisition
13. Blood collected for mRNA, proteomic and metabolomic analysis.
14. DNA to determine SMN2 copy number.
15. DNA to determine SMN1 genotyping (genetically unrelated controls only). Subjects have the option to decline this test.
16. Blood collected for SMN protein level.
17. Non-first morning void urine for proteomic and metabolomic analysis.

# STUDY MEasurements

- 1. Motor Function Assessment

The Modified Hammersmith Functional Motor Scale (15) provides a tool for evaluation of motor function in pediatric subjects with SMA type II and type III. The Modified Hammersmith Functional Motor Scale will be performed according to the Study Manual of Operations. A score of “0” is acceptable for those unable to perform any of the measurements (e.g., type I SMA subjects). In this study, both control subjects and SMA subjects will undergo the assessment as the scale is being used as the primary outcome. A minimal amount of equipment is required to perform the evaluation and the total duration is ~20 to 30 minutes to complete. Each site will have a clinically trained person performing these evaluations. It is anticipated that for control subjects, the assessment will require a minimum amount of effort and will take approximately 10 minutes to complete.

- 1. 10-meter Timed Walk Test

A 10-meter Timed Walk Test will be performed on all ambulatory SMA subjects and controls according to the Study Manual of Operations. This test compares higher functioning subjects with SMA and control subjects in their ability to walk 10 meters. (16, 17, 18)

- 1. Pulmonary Function

On subjects age >5 years, spirometry will be performed according to the Manual of Operations to measure the maximal volume of air forcibly exhaled from the point of maximal inhalation (forced vital capacity, FVC). The test will be performed 3 times in a sitting position. Subjects unable to sit may perform the FVC in a supine position and document on the appropriate CRF. Subjects who are unable to perform or complete the FVC tests may still participate in the study.

- 1. Triceps Skin Fold Thickness

The measurement of skin fold thickness of the subject’s upper arm will give an estimate of body composition and will be correlated with BMI Z score. Variability of measurement will be decreased by detailed standard procedures in the Manual of Operations and hands-on training.

- 1. Height, Weight and Ulnar Length

To calculate the BMI Z score (refer to 7.5) a subject’s height and weight is measured. Height will be measured to the nearest centimeter or tenth of an inch; weight will be measured to the nearest tenth of a pound or nearest gram. The subject is to wear light clothing with socks and shoes removed. Ulnar length will be measured because height measurement may be unreliable when neuromuscular weakness or spinal deformity is present (19). Ulnar length will be measured to the nearest centimeter or tenth of an inch as the distance between the proximal end of the ulna and the tip of the styled process. Detailed standard procedures for all these measurements are in the Manual of Operations.

- 1. BMI Z Score

The BMI Z Scale (20) is used to determine a child’s body mass index (BMI). The BMI-percentile-for-age calculator automatically adjusts for differences in height, age and gender, making it is one of the best tools for evaluating a growing child's weight. Many SMA children have a higher average BMI related to their lack of motor activity. The BMI Z Score will be automatically calculated in the Data Management System (ADEPT) upon data entering the height, weight, and ulnar length.

- 1. Specimen Collection

Up to approximately 10-mL sample of blood will be collected for gene expression (mRNA), proteomic and metabolomic analysis. All samples will be shipped and stored at the central laboratory until the end of the study where they will be shipped to the designated genomic laboratory (DNA and mRNA samples) and biomarker laboratory (plasma) for analysis. From the blood, DNA will be extracted to determine SMN2 copy number and SMN1 genotype (for genetically unrelated controls only). Please refer to the Manual of Operations for detailed processing and shipping instructions.

Up to 10-mL sample of urine will be collected for proteomic and metabolomic analysis. All samples will be shipped and stored at the central laboratory until the end of the study where they will be shipped to the designated biomarker laboratory for analysis. Please refer to the Manual of Operations for detailed processing and shipping instructions.

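### Ulnar length may be recorded to the nearest centimeter or tenth of an inch: the centimeter option is needlessly coarse for a short bone and about four times coarser than the inch option

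*Protocol*

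**What the plan says.** Protocol section 7.5 (Height, Weight and Ulnar Length) gives the reason for the measure: "Ulnar length will be measured because height measurement may be unreliable when neuromuscular weakness or spinal deformity is present". It then sets the resolution: "Ulnar length will be measured to the nearest centimeter or tenth of an inch". Standing height gets the same grid: "Height will be measured to the nearest centimeter or tenth of an inch". Weight gets a much finer one: "weight will be measured to the nearest tenth of a pound or nearest gram". Detailed procedures are referred to the Manual of Operations, which is not at hand.

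Section 11.2 (Statistical Analysis) lists height, weight, triceps skin fold, ulnar length and a nutritional question as the nutritional secondary outcomes. Continuous secondary outcomes are to be analysed by univariate and elastic net regression on the biomarkers. Section 11.5 says that age is controlled for in all models.

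The inputs to the BMI Z score are described twice. Section 7.5 says: "To calculate the BMI Z score (refer to 7.5) a subject’s height and weight is measured". Section 7.6 says that the score is "automatically calculated in the Data Management System (ADEPT) upon data entering the height, weight, and ulnar length". Its only stated analytic use, in section 7.4, is a correlation with skin fold thickness; section 11.2 does not list it as an outcome.

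**The concern.** The protocol brings in ulnar length to cover children whose height cannot be trusted, then records it on a grid suited to standing height. The ulna is a fraction of body height, so the same 1 cm is a much larger relative error on it. The text also allows two units without saying who chooses. The precision of a secondary outcome then depends on whether the person measuring works in centimeters or inches.

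Two uses are affected. As an outcome, ulnar length is correlated with biomarkers, and rounding weakens those correlations. As a possible stand-in for height, its rounding error is multiplied by the height-to-ulna slope and then roughly doubled in relative terms, because BMI divides by height squared. Each child has one visit, so precision lost at recording cannot be recovered.

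**Working it through.** The protocol gives no figure to reproduce here, so the check is a propagation of rounding error.

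**Inputs from section 7.5.** The grid g is 1 cm, or 0.1 inch = 0.254 cm. The ratio is 1/0.254 = 3.94.

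**Assumptions (not in the protocol, so ranges are shown).** The SD s of ulnar length after adjustment for age and sex is 0.7 to 1.3 cm. Height is 85 to 150 cm at ages 2 to 12. The conversion is 3 to 6 cm of height per cm of ulna.

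**Step 1, rounding error.** The maximum error is g/2 and the SD is g/√12.
- Metric: maximum 0.5 cm, SD 1/3.464 = 0.289 cm.
- Inch: maximum 0.127 cm, SD 0.254/3.464 = 0.073 cm.

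**Step 2, ulnar length as an outcome.** Reliability = s²/(s² + g²/12). A correlation is multiplied by the square root of the reliability.

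| s (cm) | Reliability, 1 cm | Loss in correlation | Reliability, 0.1 inch | Loss in correlation |
|---|---|---|---|---|
| 0.7 | 0.49/(0.49 + 0.0833) = 0.855 | 7.6% | 0.989 | 0.5% |
| 1.0 | 1/(1 + 0.0833) = 0.923 | 3.9% | 0.995 | 0.3% |
| 1.3 | 1.69/(1.69 + 0.0833) = 0.953 | 2.4% | 0.997 | 0.2% |

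For weak correlations the information scales with the squared correlation. If all 100 SMA children were measured in whole centimeters, they would carry roughly the information of 85 to 95 children measured without rounding. With a 0.1 cm grid (g²/12 = 0.00083) the loss in correlation is at most 0.1%.

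**Step 3, ulna-derived height in BMI, if that is done.** Relative BMI error ≈ 2 × slope × (g/2) / height.
- 1 cm grid: lowest 2 × 3 × 0.5/150 = 2.0%; highest 2 × 6 × 0.5/85 = 7.1%.
- 0.1 inch grid: 2 × 3 × 0.127/150 = 0.5% to 2 × 6 × 0.127/85 = 1.8%.
- 0.1 cm grid: 2 × 3 × 0.05/150 = 0.2% to 2 × 6 × 0.05/85 = 0.7%.

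These are maximum errors. Using the SD of 0.289 cm instead of 0.5 cm, the metric figures are 2 × 3 × 0.289/150 = 1.2% to 2 × 6 × 0.289/85 = 4.1%.

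**Step 4, comparison with rounding height itself.** On the 1 cm grid, 2 × 0.5/150 = 0.7% to 2 × 0.5/85 = 1.2% of BMI. The same rounding costs several times more when it passes through the ulna, by the factor of the slope.

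**Step 5, BMI Z inputs side by side.** Section 7.5 names height and weight; section 7.6 names height, weight and ulnar length. BMI needs one length. Neither section says which one enters or by which conversion. The cross-reference in section 7.5 also points to itself, whereas the contents list puts BMI Z at 7.6.

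**The case against.** The fairest reply is that this is a small matter in an exploratory pilot. A 2% to 8% loss in a correlation is modest, the inch option is already fine enough, and the SD, slope and height range all come from outside the protocol. The 2% to 7% of BMI is a maximum error and applies only if height is in fact derived from the ulna. All of that stands, and it limits the weight of the point.

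A second reply is that the Manual of Operations, with hands-on training, holds the detail. That answers any missing conversion formula, but not the resolution, which the protocol itself states. A finer instruction in the Manual would contradict it.

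A reader might go further and infer that BMI Z still rests on the height that the protocol distrusts, so that its error rises with severity. The documents do not support this. Section 7.6 names ulnar length among the entries for the calculation, so which length is used is unsettled. The two BMI problems are also alternatives for any one child: if height is used, ulnar rounding is irrelevant; if the ulna is used, height error is irrelevant. Nor does rounding error grow with severity; it depends on the grid and, in relative terms, on the length of the bone. Finally, BMI Z is not a listed outcome, so a claim that a marker of severity would pass for a marker of nutrition through BMI has no specified analysis behind it.

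**Conclusion.** The point holds for resolution, as a minor and nearly costless improvement. Section 7.5 allows two grids that differ 3.94-fold, and the 1 cm option is coarse for the ulna. It costs about 2% to 8% of any correlation with ulnar length (assumed adjusted SD 0.7 to 1.3 cm), against under 1% on the inch grid. It would cost at most about 2% to 7% of BMI if height is derived from the ulna (assumed slope 3 to 6, height 85 to 150 cm). If some children are measured in each unit, the overall loss lies between the two grids.

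The different descriptions of the BMI Z inputs in sections 7.5 and 7.6 are a secondary point of wording. They do not show that the score is computed wrongly. The primary outcome and the sample size are not affected.

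**What to change.** In section 7.5, require ulnar length and height to the nearest 0.1 cm at every site, and bring the Manual of Operations into line. The gain lies mainly in ulnar length; height is included so that one unit and one rule apply to both. The cost is a changed field format on the CRF and in ADEPT and a line in the training. No extra measurement is needed.

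As a clarification, state once, in section 7.5 or 7.6, which length measure enters the BMI Z score and by which named conversion, and correct the cross-reference. The choice is left to the study team. One trade-off deserves attention: using ulna-derived height only in non-ambulatory children or those with spinal deformity would make the method depend on severity, so any bias in the conversion would be confounded with SMA type.
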